### Intervention and control conditions

There will be two levels of electronic game access. 'No active electronic games' will involve all active input electronic games being removed from the family home with a contract that active electronic games will be avoided where possible at other locations. Participants will be able to play traditional electronic games using a game pad input during this period. 'Active electronic games' will involve the provision of a Sony PlayStation 3 with Move and Eye input devices and Microsoft Xbox360 with Kinect input device and a range of non-violent games. Children will be contacted regularly during the study and asked to report exposure to electronic games including games played, frequency and duration and level achieved. Children will also be asked about participation in other activities such as sports and hobbies.

A condition period of 16 weeks will allow time for improvements in motor impairment during the active electronic games condition whilst fitting in with school holiday schedules. A within subjects design allows reduced study numbers.

### Outcome measures

#### Motor coordination

Motor coordination will be assessed using the MABC-2 and during a series of tasks performed in a motion analysis laboratory. Detailed kinematic and kinetic data will be collected using a three-dimensional motion analysis system (Vicon; Oxford Metrics, inc.) and two AMTI force plates (Advanced Mechanical Technology, inc.). The large (0.6 * 1.2 m) and small (0.6*0.3 m) force plates are located in the middle of the laboratory directly next to one another and will be operated at 1000 Hz. The 14 camera Vicon motion analysis system will be calibrated to collect data in an approximately 5 m^2 ^area in the middle of the laboratory, running at 250 Hz. Prior to trial performance each child will be fit with the custom full body marker set (seventy two 14 mm retro-reflective markers). This marker set (Table 1) follows a cluster based protocol and allows the accurate calculation of full body joint kinematics and kinetics complicit with the International Society of Biomechanics recommendations [61,62].

**Table 1 T1:** Three-dimensional motion analysis marker set

Marker	Anatomical location	Real (R) or Virtual (V)*
**Head markers**		

Eye markers	Placed lateral to canthus of the left and right eyes	R

Ear markers	Placed above the tragus (or concha) of the left and right ears	R

Nose marker	Placed on the tip of the nose	V

**Thorax/Back markers**		

Anterior thorax marker	Sternal notch between the two clavicles	R

Posterior thorax markers	Placed on the 7^th ^cervical and 6^th ^thoracic vertebrae	R

**Pelvis:**		

Anterior pelvis	Right and left anterior superior iliac crests	R

Posterior pelvis	Right and left posterior superior iliac crest	R

**Lower limbs**		

Thigh markers	Three markers set on a t-bar cluster, with the long bar fixed mid-segment along the iliotibial band. The short bar raps medially onto the quadriceps.	R

Tibia markers	Three markers set on a t-bar cluster, with the long bar fixed mid-segment along the tibia. The short bar raps laterally towards the fibula.	R

Knee markers	Four markers placed on the right and left, medial and lateral femoral condyles	V

Feet markers	Three markers placed on the calcaneus, talus hook and 5^th ^metatarsal	R

Ankle markers	Four markers placed on the right and left, medial and lateral malleoli	V

**Upper limbs**		

Shoulder markers	Right and left, anterior and posterior shoulder markers	V

Right and left acromion markers	Three markers placed on the posterior and anterior portion of the lateral border of the acromial plateau, with one marker placed laterally at the base of the acromioclavicular joint.	R

Right and left upper arm markers	Three markers set on a t-bar cluster, with the long bar fixed mid-segment on the lateral aspect of the upper arm. The short bar raps laterally towards the biceps.	R

Elbow markers	Right and left, medial lateral epicondyle markers	V

Forearm markers	Three markers placed on the medial and lateral aspect of the distal third of the forearm, with one marker placed mid segment - between the radius and ulnar, midway up the forearm.	R

Wrist markers	Right and left, medial and lateral wrist markers placed on the ulnar and radial styloid processes	V

Hand markers	Three markers, two placed mid-hand medially and laterally. The third marker is placed directly below the junction between the third metacarpal and third proximal phalange.	R

Finger markers	Two smaller markers (5 mm diameter) fixed to the most distal portion of the index finger, finger nail	R

**Equipment**		

Ball markers	Three markers fixed to each ball; tennis ball, t-ball ball, soccer ball	R

T-ball bat tip	A single marker fixed to the tip of the t-ball bat	R

* 'Virtual' markers are removed after one static trial. 'Real' markers remain throughout the motion analysis data collection

Three tasks drawn from common motor performance tools will be used to assess whole body coordination: running, single leg stance and horizontal jump. Running will be performed using the Test of Gross Motor Development, 2^nd ^edition (TGMD-2; [63]) protocol which involves running over the 10 meter laboratory runway with children instructed to run as fast as they can. Five trials will be performed. Trials will be deemed successful if the child strikes one of the force platforms with their preferred leg. The starting point of the runway will be adjusted in the instance successful foot strike does not occur and the child will not be informed of this requirement to facilitate natural running technique. Single leg stance will be performed using the MAND [46] protocol which involves balancing on their preferred foot with the arms free to move for balance, the unused leg held off the floor with slight knee flexion and pivoting allowed but hopping not. Children will be instructed to stand on the large force plate on their preferred foot for as long as they can or until told to stop. Two trials will be completed with a maximum period of 30 seconds for each trial. Horizontal jump will be performed using the TGMD-2 protocol which involves jumping with feet parallel at start and finish. Children will be instructed to jump as far as they can, while 'sticking' their landing and will perform 5 trials. The take-off will be performed from the middle of the small force plate.

Four tasks drawn from common motor performance tools will be used to assess limb coordination: finger-nose, ball strike, ball kick and ball bounce and catch. Finger-nose touch will be performed using the MAND protocol which involves children holding their non preferred arm out in front at shoulder level with the index finger pointed at right angles. The index finger of their preferred hand is used to touch the tip of their nose and the tip of the extended finger moving from supination to pronation. The children will be instructed that it is not a speed test. Ten trials will be performed. Ball strike will be performed using the TGMD-2 Tee ball task which involves a ball being placed on a tee at the height of the child's waist and struck with a bat. The child will be instructed to place their feet shoulder width apart, one on each force plate, facing perpendicular to the intended direction of the t-ball strike and then to hit the ball hard. This task will be repeated 5 times. Ball kick will be performed using the TRMD-2 soccer kick task which involves a ball being positioned on the ground slightly ahead (next to the small force plate) and to the preferred side. Children will be instructed to step forward, from the large force plate onto the small force plate, using their non preferred foot and kick the ball as hard as they can towards a goal. The task will be performed 5 times. The ball bounce and catch task is based on the TGMD-2 ball bounce task and requires the participant to stand on the large force plate and bounce the ball onto the small force plate. Children will be instructed to drop the ball with their preferred hand and catch it with both hands.

Four tasks will be used to assess coordination during active electronic game performance: Move table tennis, Move archery, Kinect table tennis and Kinect soccer penalty kick. For each electronic game task children will be instructed how to perform the task then allowed to practice the task a standard number of times specific to each game. Table tennis will be performed against a computer opponent, with 5 practice points and one game to 11 points repeated on both electronic game consoles. Move archery will be performed against a computer opponent for three trials of 45 seconds. The first set will be used as practice and the final two as assessment trials. The penalty kick trials, performed against a computer opponent, will include one practice trial and three assessment trials.

The primary outcome measures will be the MABC 2 Total Impairment Score, balance as characterised by the length of the path of the centre of mass during the single leg stance trial [28], and upper limb control as characterised by the normalised length of the trajectory of the finger in the finger-nose task [64].

Additionally, movement variability will be assessed using the standard deviation of magnitude and rate of change of kinematics and kinetics across the multiple trials of each task; movement smoothness will be assessed using motion pathway rate of change and jerk [65]; movement efficiency will be assessed using time to stability, out of plane motion and path distance; movement sequencing will be assessed with kinematic chain coupling and time of segmental movement onset; and movement accuracy will be assessed using target error distance. Game performance will also be recorded.

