## Methods/design

### Design and Aims

This study will use a cross over randomised controlled trial to assess the impact of active electronic game use on motor coordination and physical and mental health correlates in children with DCD by:

1) Comparing change in motor coordination over 16 weeks when children use active electronic games or no active electronic games. We hypothesise that motor coordination will improve more when children use active electronic games.

2) Comparing change in parent reports of motor coordination during activities of daily living over 16 weeks when children use active electronic games or no active electronic games. We hypothesise that parent reports of motor coordination will improve more when children use active electronic games.

3) Comparing change in physical activity and sedentary behaviour over 16 weeks when children use active electronic games or no active electronic games. We hypothesise that moderate/vigorous physical activity will increase and sedentary time will decrease more when children use active electronic games.

4) Comparing change in attitudes to physical activity over 16 weeks when children use active electronic games or no active electronic games. We hypothesise that attitudes to physical activity will improve more when children use active electronic games.

5) Comparing change in child reports of mental health over 16 weeks when children use active electronic games or no active electronic games. We hypothesise that mental health will improve more when children use active electronic games.

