### Sample

30 children (10-12 years of age) will be recruited by mass media, university and school notices and professional networks. This age group has been selected as they are able to provide detailed information in diary and questionnaires, have a high use of electronic games and are developing physical and mental behaviour patterns pre-puberty which may track into adulthood. Children of parents expressing interest will be screened to ensure they are willing to participate after being informed of the full study responsibilities and meet the inclusion and exclusion criteria. Inclusion criteria are: aged 10-12 years at start of study, able to use electronic games on most days and being classified as DCD. DCD status will be assessed using Movement Assessment Battery for Children-2 (MABC-2 [56]. The MABC-2 comprises 8 tasks, three measuring manual dexterity, 3 measuring aiming and catching and 2 measuring balance. Age norms based on a standardisation sample of 1,172 children are used to determine a standard total score (*M *= 10, *SD *= 3). Separate standard scores can be determined for each of the sub-tests. In addition to the total score, a set of qualitative observations allows the examiner to record the child's performance characteristics during the testing. Cut-offs for impairment scores are at or below the 5th percentile for definite motor difficulties, whilst scores above the 5th percentile but at or below the 15th percentile suggest borderline difficulties. The 15^th ^percentile cut off will be used in this study as this is recommended for research purposes to prevent excluding children with mild DCD [57]. Minimum value of the test-retest reliability of the original MABC is 0.75 and the inter-tester reliability is 0.70. The original MABC has been found to correlate well with other movement tests [58,59]. The MABC-2 will be conducted at a location agreed to by parents, typically the child's home. Children will be excluded if they have a diagnosed disorder likely to impact their study participation, movement or electronic game use (other than developmental coordination disorder), live in a shared care arrangement where the child spends a significant amount of time in different houses and is unable to maintain game access condition, or live remote to the University campus. The child's age and sex will be recorded at baseline along with their experience with electronic games and computers using the Young people's Activity Questionnaire [11].

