For power calculations, motor impairment (MABC-2 Total Impairment Score) was estimated at 17+5 with a minimum effect size of 5 considered important based on effects in prior studies [60]. If the variation in the motor impairment between repeated time points in each individual is normally distributed with standard deviation 5, and the true effect of game condition is 5, a study with 30 subjects will reject the null hypothesis that this response difference is zero with probability (power) 0.9027. The Type I error probability associated with this test of this null hypothesis is 0.01.

Volunteers and their parents will be provided with a detailed written description of the study purpose, procedures, risks and benefits and given an opportunity to ask research staff for clarification prior to signing assent (children) and consent (parents) to participate. The study has ethical approval from the Human Research Ethics Committee of Curtin University (approval number HR11/2011).

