### Analysis

To examine hypothesis 1 (that motor coordination will be improved when children have access to active electronic games) changes from baseline in laboratory biomechanical and MABC-2 outcomes following both conditions will be compared with a repeated measures ANCOVA analysis with sex as a covariate. A critical alpha level of 0.01 will be used to balance type 1 and type 2 errors.

To assess hypotheses 2, 3, 4, 5 (that parent reports of motor coordination in daily living, physical activity and sedentary behaviour, attitudes to physical activity and measures of mental health will improve when children have access to active electronic games) changes from baseline in outcomes following both conditions will be compared with a repeated measures ANCOVA analysis with sex as a covariate. A critical alpha level of 0.01 will be used to balance type 1 and type 2 errors.

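### The balance primary outcome is centre-of-mass path length over a stance of variable duration with no time scaling, so a true balance gain can be diluted or reversed in sign

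*Protocol article*

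**What the plan says.** Under Outcome measures, Motor coordination, the protocol article names three primary outcomes: the MABC-2 Total Impairment Score, "balance as characterised by the length of the path of the centre of mass during the single leg stance trial", and "upper limb control as characterised by the normalised length of the trajectory of the finger in the finger-nose task".

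The task description in the same section sets how long a stance trial lasts. The child stands "on their preferred foot for as long as they can or until told to stop", and "Two trials will be completed with a maximum period of 30 seconds for each trial". The text shown gives a maximum but no minimum, no common analysis window and no rule for scoring a trial that ends early.

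Under Analysis, changes from baseline "following both conditions will be compared with a repeated measures ANCOVA analysis with sex as a covariate". Stance time does not enter the model. Under Design and Aims the expected direction is stated: "We hypothesise that motor coordination will improve more when children use active electronic games". The article never says outright that a shorter centre-of-mass path is better; that is implied by using it as a measure of balance.

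**The concern.** Trial duration is itself a result of the child's balance, and path length accumulates over that duration. The two ways in which balance can improve therefore push the score in opposite directions: swaying more slowly shortens the path, and standing longer lengthens it.

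The population makes this relevant. Under Sample, "The 15^th ^percentile cut off will be used in this study", applied to the MABC-2, a battery with two balance tasks. Stances shorter than 30 s at baseline, with room to lengthen, are plausible. If active games help in the way hypothesis 1 predicts, stance may lengthen in the active condition, and the primary balance outcome would then understate the benefit or show it as harm.

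**Working it through.** **The article's own figure.** The only computed design figure is the power of 0.9027 under Sample, for the MABC-2 Total Impairment Score "with a minimum effect size of 5 considered important based on effects in prior studies". It reproduces with a normal approximation, two-sided alpha 0.01 and a standard deviation of the within-child difference of 5 × √2 = 7.07:

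- standard error = 7.07 / √30 = 1.291
- 5 / 1.291 = 3.873, and 3.873 − 2.576 = 1.297
- Φ(1.297) = 0.9027

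This figure concerns the MABC-2 only. No power or effect size is given for the balance outcome, so the check below is algebraic, with illustrations.

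**Break-even.** Let L be path length, t stance time and v = L / t mean sway speed. Then L = v × t, and

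L1 / L0 = (v1 / v0) × (t1 / t0).

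If speed falls by a fraction d, the path gets longer whenever t1 / t0 > 1 / (1 − d).

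| Fall in sway speed | Break-even t1 / t0 | Path increases if stance is longer by more than |
|---|---|---|
| 10% | 1 / 0.9 = 1.11 | 11% |
| 20% | 1 / 0.8 = 1.25 | 25% |
| 30% | 1 / 0.7 = 1.43 | 43% |

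**Illustrations.** The stance times and speed changes are assumptions; the article gives none.

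| Stance time | Fall in speed | Raw path ratio | Raw path | Path per second |
|---|---|---|---|---|
| 20 s to 30 s | 20% | 30 × 0.8 / 20 = 1.20 | +20% | −20% |
| 12 s to 18 s | 10% | 18 × 0.9 / 12 = 1.35 | +35% | −10% |
| 25 s to 28 s | 20% | 28 × 0.8 / 25 = 0.90 | −10% | −20% |
| 30 s to 30 s | 10% | 30 × 0.9 / 30 = 0.90 | −10% | −10% |

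The first two rows reverse sign. The third keeps the right sign but shows half the effect. In the fourth, both trials reach the cap and the two measures agree.

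**Simulation of the trial-level effect.** Assumptions: 30 children; within-child comparison of the two conditions by paired t test at two-sided 0.01; median control sway speed 40 mm/s; a true benefit of 10% lower speed and 40% longer stance before capping; stance capped at 30 s. Log-scale standard deviations were 0.25 between and 0.15 within children for speed, and 0.5 between and 0.3 within for stance time. There were 3,000 replicates per row.

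| Median stance before capping | Control trials at 30 s | Mean raw path change | Wrong direction, p < 0.01 | Right direction, p < 0.01 |
|---|---|---|---|---|
| 8 s | 1% | +91 mm | 31% | 0% |
| 12 s | 6% | +103 mm | 25% | 0% |
| 20 s | 24% | +66 mm | 6% | 0% |
| 30 s | 50% | −3 mm | 0.4% | 1% |
| 60 s | 88% | −102 mm | 0% | 25% |
| 120 s | 99% | −123 mm | 0% | 43% |

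In the same replicates, path per second was significant in the right direction in 45% to 48% of trials in every row. The result for raw path depends almost entirely on how many trials reach the cap.

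**The case against.** **The absence of scaling is inferred.** The definition is one line with a citation. The cited source or a full protocol might set a window or a scaling, and an article commonly leaves processing detail to such documents. That is fair, and it is why how the two trials are combined is not raised here. It does not remove the point: the article states a primary outcome and a variable-duration task, and following both as written mixes steadiness with endurance.

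**The contrast with the finger-nose outcome.** A reader might infer, because that trajectory is called normalised, that the authors scaled one outcome for time and knowingly left the other unscaled. The text does not support this. It does not say what the finger trajectory is normalised to; it could be a distance. The point does not rest on that word.

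**Reversal is not automatic.** A reader might infer that any child who balances longer scores worse. That is too strong: stance must lengthen by a larger factor than speed falls. The children are 10 to 12 years old, with arms free and pivoting allowed, so many may reach 30 s. This stands in full.

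**Constant speed.** Corrective movements before a loss of balance could add path to short trials and offset part of the artefact. L = v × t holds exactly with v as mean speed, but the illustrations do treat speed and duration as separately adjustable.

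**Within-child comparison.** Stable differences in stance time between children largely cancel. Only a change in duration that differs between conditions matters. That is correct, but such a change is what a successful intervention could produce.

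**Other information.** The MABC-2 score includes two balance tasks and is unaffected, and rate-of-change measures of the motion path are planned across tasks, though not as primary outcomes.

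**Conclusion.** The point holds as a defect in the stated definition. As written, the balance primary outcome can dilute a true gain or reverse its sign, and the planned model, with sex as its only covariate, does not correct for this. Reversal requires stance to lengthen by more than 11%, 25% or 43% for a 10%, 20% or 30% fall in sway speed.

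The size in this trial cannot be stated, because it depends on stance times that the article does not give. Under the assumed benefit in the simulation, the mean raw path moved the wrong way at median stances of 8 to 20 s, was about zero at 30 s, and had the right sign once 88% or more of control trials reached the cap. If nearly all trials last 30 s, nothing is lost.

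A reader might infer that one third of the primary evidence is uninterpretable. The document does not support that: it would require durations mostly well below the cap, and the other two primary outcomes are untouched. The conclusion also assumes that a shorter path is meant as better and that no unseen document already fixes a window or a scaling.

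**What to change.** Define the primary balance outcome as centre-of-mass path length divided by stance time (mean centre-of-mass speed), with lower values meaning better balance. Report stance time, capped at 30 s, beside it as a supporting measure.

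If path length over a fixed common window is preferred, state the window and how a trial shorter than it is scored; otherwise the same problem returns for early failures.

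The choice should be made before outcome data are seen, so that it cannot follow the results. The cost is one or two sentences. The same recordings are used, and the sample size, which was set on the MABC-2, does not change. The small downside is that speed alone does not capture endurance, which is why stance time is reported with it.
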